## Abstract

**Background:**

The prevalence of overweight and obesity is on the rise worldwide with severe physical and psychosocial consequences. One of the most dangerous is hypertension. Lifestyle changes related to eating behaviour and physical activity are the critical components in the prevention and treatment of hypertension and obesity. Data indicates that the usual procedures to promote these healthy habits in health services are either insufficient or not efficient enough. Internet has been shown to be an effective tool for the implementation of lifestyle interventions based on this type of problem. This study aims to assess the efficacy of a totally self-administered online intervention programme *versus* the usual medical care for obese and overweight participants with hypertension (from the Spanish public health care system) to promote healthy lifestyles (eating behaviour and physical activity).

**Method:**

A randomized controlled trial will be conducted with 100 patients recruited from the hypertension unit of a public hospital. Participants will be randomly assigned to one of two conditions: a) SII: a self-administered Internet-based intervention protocol; and b) MUC-medical usual care. The online intervention is an Internet-delivered, multimedia, interactive, self-administered programme, composed of nine modules designed to promote healthy eating habits and increase physical activity. The first five modules will be activated at a rate of one per week, and access for modules 5 to 9 will open every two weeks. Patients will be assessed at four points: before the intervention, after the intervention (3 months), and at 6 and 12 months (follow-up). The outcome variables will include blood pressure, and Body Mass Index, as primary outcome measures, and quality of life and other lifestyle and anthropometrical variables as secondary outcome measures.

**Discussion:**

The literature highlights the need for more studies on the benefits of using the Internet to promote lifestyle interventions. This study aims to investigate the efficiency of a totally self-administered Internet − +based programme for promoting healthy habits and improving the medical indicators of a hypertensive and overweight population.

**Trial registration:**

NCT02445833

## Background

Lifestyle is one of the most important determinants of health. Since most communicable diseases are largely controlled in Western countries, current health problems are mainly related to behavioural variables [1], and most diseases are significantly influenced by lifestyle. Sedentary behaviour, consumption of fatty foods, fast foods, alcohol or tobacco, and stress, among other factors, are important causes of mortality and disease [2], and they have a determining influence on the maintenance of chronic diseases, including high blood pressure (hypertension) and obesity.

The World Health Organization [3] considers hypertension to be one of the most important public diseases in the world. This non-communicable disease is responsible for over a third of deaths from cardiac causes [4], and its costs are increasing alarmingly [5, 6]. The usual treatment for hypertension is based on medical-pharmacological interventions, however, evidence shows that changes in habits and lifestyles are crucial for treating this disease [3].

Obesity and being overweight (Body Mass Index: BMI ≥ 25 kg/m2) are also considered important health problems, due to their high prevalence, their multiple negative consequences, and their high costs [7, 8]. Although several factors are involved in their aetiology, evidence points to diet and physical activity as critical in both the prevention and treatment of obesity and associated disorders [9].

Hypertension and obesity are frequently associated. Overweight and obesity contribute to the occurrence of hypertension through different mechanisms, and weight loss is related to a drop in blood pressure. Evidence shows that blood pressure begins to drop in hypertensive obese patients they reach their ideal weight [10, 11].

Interventions in lifestyles are frequently recommended for both hypertension and obesity, however, these kinds of treatments collide with the problem of motivation, and environmental and personal barriers that often hinder their implementation. Non-adherence rates are usually very high for both obesity and hypertension [12], pointing out the need to develop alternative strategies to promote adherence and the success of lifestyle interventions. Although some interventions are effective in producing behavioural changes [13], these changes are generally moderate [14] and followed by a decline over time [15]. To improve outcomes in the medium and long term, there has been a proposal to adapt the interventions to the idiosyncratic characteristics of each person, emphasising the importance of providing constant and immediate feedback throughout the intervention [15]. Along these lines, and especially for chronic diseases, recent approaches to dispensing health services propose that these solutions should focus on the individual, providing information, services and tools that help them to implement and maintain behaviours related to health [16]. The objective is to replace previous models, focused on disease, with a more proactive approach to health, centred on welfare. This approach “empowers” the person by developing tools and services that people like, want, and can use, to achieve the necessary skills to respond appropriately in health-related situations [17].

To achieve these objectives, Information and Communication Technologies (ICTs) are a promising alternative, because they make it possible to provide personalised feedback [18] and they can be adapted flexibly to each user [19]. ICTs also have other important advantages, especially their good cost-benefit relationship and the possibility of increasing the efficiency of interventions, allowing them to reach a wider audience at a lower cost [20]. Interventions for hypertension and obesity could benefit from a shift in this direction, and there is evidence supporting the efficacy of online interventions for these conditions.

Regarding interventions for obese individuals, Levine et al. [21] reviewed the studies of technology-assisted weight loss interventions specifically provided in primary care settings, and the results showed that they helped patients achieve significant weight loss, giving participants the option to undergo the intervention semi-remotely. The authors concluded, however, that longer, pragmatic, interdisciplinary, open-source interventions are needed. In a similar way, meta-analyses performed by Neve et al. [22], Manzoni et al. [23], Kodama et al. [24], and Dutton et al. [25] found that Internet use in obesity treatment programmes has a modest but significant effect on weight control. These reviews also point out variations between trials (with smaller effect sizes, and inconsistent findings across studies), mixed results, heterogeneity of designs, and low generalization of the findings, however, and they emphasise that better descriptions of components of effective interventions are still needed. It is also necessary to develop and evaluate Internet-based weight-loss interventions that are specifically tailored to the needs of the health-care delivery system [23].

Regarding Internet-based lifestyle interventions for hypertension, studies that analyse and compare them with standard treatments are still scarce. In a recent systematic review, Vegting et al. [26] evaluated whether Internet-delivered care, as a complement to the usual care, improved cardiovascular outcomes. Nine studies were found, and only three specifically addressed hypertension [27–29]. Two of them found a significant decrease in BMI/weight [27, 29] and blood pressure (BP) measures [28, 29] in the intervention group compared to the control groups. More research is therefore needed in order to draw stronger conclusions about use of the internet in hypertension programmes.

In summary, Internet-based interventions are promising tools to promote a healthy lifestyle in people who are overweight or obese, and they can be of value in treating people who have hypertension and are at risk of developing metabolic syndrome. An intervention specifically for hypertensive obese patients, which is focused on changing their lifestyle, delivered over the Internet, and implemented in a public health context could be a cost-effective and affordable measure for reducing high blood pressure (BP).

The main objective of this study is to design, develop and test a completely self-administered Internet-based programme to promote healthy habits (diet and physical activity) in hypertensive patients with overweight or type I obesity who are at risk of developing diabetes mellitus. This programme will last three months, and it will be implemented in a public hospital service (a hypertension unit). The impact of this three-month programme will be analysed based on levels of BP, BMI, quality of life and other variables, and the results will be compared to a control group receiving their usual medical care.

## Method

### Study design

This is a two-armed, single centre, comparative, randomized controlled trial, comparing two conditions: a) a self-administered Internet-based intervention (SII) and b) usual medical care (UMC). The study will be conducted following the CONSORT statement (Consolidated Standards of Reporting Trials, http://www.consort-statement.org) [30, 31] and CONSORT-EHEALTH guidelines [32].

### Setting and study sample

The clinical trial will be conducted in the Hypertension and Vascular Risk Unit of the Hospital de Sagunto in Valencia (Spain). Participants will be recruited by physicians working in this unit. Participants should meet the following criteria: overweight or obese grade I (BMI > 25 and <35); age between 18–65 years; in clinical medical treatment for the prevention of metabolic syndrome or cardiac complications. Exclusion criteria are: no Internet access; taking more than three antihypertensive drugs; a diagnosis of diabetes; meeting the DSM-5 criteria for an eating disorder; having a disability that prevents or hinders exercise and physical activity; receiving any treatment for weight loss elsewhere.

### Sample size

The sample size for this project was based on the effect size found in previous studies [23, 33–35]. In previous RCT online interventions [33] a moderate effect size (g = 0.64) was found [23] when evaluating bodyweight. Taking this into account, a conservative effect size of .64 (Cohen’s d = .64) is expected in primary outcome measures. An estimation of the desired sample size was made based on the expected difference in the primary outcome variables, BP, BMI. Based on a power of 0.80 in a one-tailed test and an alpha of 0.05, 30 participants in each condition would be required. Considering the high levels (around 30 %) of dropout observed in this type of intervention [36], we chose to increase the expected sample to 50 participants in each condition. The hospital where the study took place selected a list of possible patients based on the inclusion and exclusion criteria.

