### Statistical data analysis

SPSS v.20 will be used for statistical analysis. Relevant statistical analyses will first be performed to verify proper randomization (independent samples *t* test for equivalence of groups). Intention-to-treat and per-protocol analysis will be used. Descriptive statistics for the variables included (mean and 95% confidence interval for normally distributed quantitative variables; and median and interquartile range for abnormally distributed quantitative variables) will be performed. A series of repeated-measures mixed ANOVAs with planned contrasts (2×2) will be carried out: with intergroup variable (condition - OI × UMC) × intragroup variable (time - pre- and post-) for each dependent variable. More sophisticated multivariate analysis, including multilevel regression, will be used. The effect size of improvement and intention-to-treat (ITT) will be estimated.

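### The 80% power figure rests on an unjustified one-tailed 0.05 test that the planned 2×2 mixed ANOVA does not apply; two-sided power is about 75% with 35 completers per arm

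*Protocol article*

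**What the plan says.** In the protocol article, the Sample size section takes a published g of 0.64 for bodyweight and carries it over unchanged: "a conservative effect size of .64 (Cohen’s d = .64) is expected in primary outcome measures". The primary outcomes are blood pressure and BMI. The requirement is then given as "Based on a power of 0.80 in a one-tailed test and an alpha of 0.05, 30 participants in each condition would be required". Because about 30% dropout is expected, enrolment is raised to 50 per condition. No reason is given for testing in one tail.

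The Statistical data analysis section plans "A series of repeated-measures mixed ANOVAs with planned contrasts", with condition (two levels) crossed with time (pre and post), for each dependent variable. It mentions both intention-to-treat and per-protocol analyses. It gives no alpha, no sidedness and no directional hypothesis for these tests.

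**The concern.** The sample size and the analysis appear to refer to different tests. The condition × time interaction in a 2×2 mixed ANOVA has one numerator degree of freedom. Its F statistic is the square of the t statistic that compares mean change between arms, so a large F arises from a difference in either direction. Judged at 0.05 in the usual way, this is a two-sided test, and its critical value is stricter than the one used to size the trial.

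If the 80% figure is carried into the trial report beside two-sided p-values, a null result on blood pressure or BMI will be read as coming from a better-powered trial than was run. If instead a one-tailed 0.05 test is really meant, the chance of falsely declaring benefit is 5% rather than the 2.5% implied by a two-sided 0.05 test, and that choice should be stated and defended. Only one of these consequences can apply. The article does not let the reader tell which.

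**Working it through.** **Inputs, all from the Sample size section:** d = 0.64; alpha 0.05, one-tailed; power 0.80; 30 required per arm; about 30% dropout; 50 enrolled per arm. The tested contrast (condition × pre/post, 1 df) comes from the Statistical data analysis section.

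**Step 1. Reproduce the plan's figure.** By the normal approximation, n per arm = 2(z₁₋α + z₁₋β)² / d².

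- One-sided: 2 × (1.645 + 0.842)² / 0.64² = 30.2, that is, 30 to 31 per arm.
- The exact noncentral-t calculation gives 31, and 79.0% power at 30 per arm.

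The stated 30 is therefore reproduced, within rounding, as a one-sided calculation. The dropout allowance is also ample on those inputs. 30 / 0.7 = 42.9, so 43 per arm would do. With 50 enrolled, 50 × 0.7 = 35 complete, and one-sided power at 35 is 84.3%.

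**Step 2. Repeat for a two-sided test.** The normal approximation gives 2 × (1.960 + 0.842)² / 0.64² = 38.3, that is, 39 per arm. The noncentral t gives 40. Power uses noncentrality d√(n/2) on 2n − 2 df:

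| n per arm | noncentrality | two-sided critical t | one-sided power | two-sided power |
|---|---|---|---|---|
| 30 (stated minimum) | 2.479 | 2.002 | 79.0% | 68.4% |
| 35 (50 less 30%) | 2.677 | 1.995 | 84.3% | 75.2% |
| 40 | 2.862 | 1.991 | 88.3% | 80.7% |
| 50 (no loss) | 3.200 | 1.984 | 93.7% | 88.7% |

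Forty completers per arm at 30% dropout means 40 / 0.7 = 57.1, so 58 enrolled, against 50 planned. With 35 completers per arm, the d detectable with 80% power is about 0.68.

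**Step 3. Scale of d.** The table applies 0.64 directly to the tested contrast. For change scores, this means that d is standardised by the SD of change or, equivalently, by the raw-score SD with a pre-post correlation r of 0.5. The article gives neither. If d is in raw-score SD units, the effect on the change scale is 0.64 / √(2(1 − r)). Two-sided power at 35 per arm is then:

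| r (assumed) | d on change scale | power |
|---|---|---|
| 0.3 | 0.541 | 61% |
| 0.5 | 0.640 | 75% |
| 0.56 | 0.682 | 80% |
| 0.6 | 0.716 | 84% |
| 0.7 | 0.826 | 93% |

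**Step 4. The planning value.** The g quoted for bodyweight is 0.64 and the planning value is 0.64. No discount appears between the two, yet the value is called "a conservative effect size of .64".

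**The case against.** The strongest reply is that nothing in the analysis section rules out a one-tailed test. A 1-df planned contrast can be tested directionally, and a later analysis plan might say so. The Sample size section also discloses its one-tailed basis openly. This stands in part: two-sidedness is inferred from the F test and is not written in the article. It does not rescue the text, because the directional choice is neither justified nor carried into the analysis, and the named method is non-directional as it is ordinarily used.

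A second reply is that intention-to-treat analysis of all 50 per arm would have about 89% two-sided power. That requires outcome data on everyone. The plan enlarges the sample because it expects to lose about 30%, and a pre/post repeated-measures ANOVA needs both measurements.

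A third reply is that a pre-post correlation of about 0.56 or more removes the shortfall if d is on the raw-score scale. This is correct, and it limits the conclusion. A lower correlation makes matters worse by the same route, and the article takes no position.

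Three stronger readings are tempting, and the document does not support them:

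- A reader might infer that the trial as designed has only 68% power. That figure belongs to the calculated minimum of 30 per arm; the design enrols 50.
- A reader might infer a miscalculation. Step 1 shows that there is none.
- A reader might infer from the Background's summary, that "Internet use in obesity treatment programmes has a modest but significant effect on weight control", that 0.64 is wrong. That sentence pools several reviews and gives no competing value. The paragraph also cites further studies, so whether 0.64 is cautious relative to those cannot be judged here. What can be said is that it equals the one value quoted.

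**Conclusion.** The concern holds as a mismatch between the power calculation and the planned analysis. On the plan's own d and dropout rate, the enrolled design has about 75% power in a two-sided 0.05 test, against the stated 80% and against the 84% that the same 35 completers would give one-tailed.

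The 75% rests on three assumptions: the ANOVA is judged two-sided at 0.05, dropouts do not contribute to the pre/post comparison, and d = 0.64 applies on the scale analysed (for change scores, r = 0.5). Under the raw-score reading, the figure could lie anywhere from about 61% to 93% for r between 0.3 and 0.7, so a shortfall is not certain. What is certain is that the sidedness of the power statement is unjustified and does not carry through to the analysis.

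**What to change.** Keep 50 per arm. Rewrite the Sample size paragraph for a two-sided alpha of 0.05: about 75% power for d = 0.64 with 35 completers per arm, and a detectable d of about 0.68 at 80% power. State whether d refers to change scores or raw scores and, if raw, which pre-post correlation is assumed. Name the same sidedness and alpha in the Statistical data analysis section. Delete the word conservative, since the planning value is the quoted g for bodyweight without any reduction.

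If a one-tailed test is truly intended, the alternative is to say so in the analysis section and justify it there.

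The cost is a few sentences and a slightly less favourable stated power. No patients or procedures are added.

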### Recruitment and randomization

Participants will be recruited from the patient database of the hospital’s Hypertension Unit. The physicians in this unit will make a selection of patients who fit the inclusion criteria, then, a letter will be sent to these patients informing them of the study and requesting cooperation. Interested patients will be given an appointment at the hospital, where they will receive more detailed information. If patients agree to participate, they will be asked for their informed consent, and after signing, allocated to one of two groups: a) *Self-administered Internet-based Intervention (SII),* or *Usual Medical Care (UMC)*. Randomization will be performed using *random allocation software*. The programme Epidat 4.1 will be used to generate this sequence. The allocation will be carried out by an independent researcher, who will be unaware of the characteristics of the study. The sequence will be concealed until interventions are assigned. Patients will agree to participate before the random allocation and without knowing to which treatment they will be allocated. Study researchers conducting assessments across the whole study will be blind to participant treatment conditions and will be unaware of the group to which any patient belongs.

### Procedure

Participants will be given an appointment at the hospital in the first week to be assessed. They will then find out their randomization condition, and the following procedure will take place:

#### For participants in the SII condition

Patients will be given an explanation of the online intervention and instructions about how to access the modules, how to use them, and how to fulfill the online questionnaires. The modules will be active for three months during the intervention.

#### For participants in Usual Medical Care (UMC)

Patients will receive an explanation of the study, and how to fill out the questionnaires. Internet-based intervention will be offered to them at the end of the study (three months after its end) if they are interested. Patients will be called by their physicians following the usual care protocol.

### Internet-based intervention

The intervention programme is called “*Vivir mejor*” (“Living better”), and it is Internet-delivered (a web-page will be developed), multimedia, interactive, self-administered programme intervention composed of nine modules designed to gradually change participants’ eating habits and physical activity. The programme will be established as follows: the first five modules will be activated at a rate of one per week, and for modules 6 to 9, access will open every two weeks. The modules are:

#### M0. Welcome

Its purpose is to welcome participants to the programme, describe what it is and its structure (9 modules), explain the objectives and the main contents, and motivate participants to start the programme.

#### M1. Motivation for change

Its aim is to offer information about the importance of motivation in changing one’s lifestyle, and help participants understand that it is possible to increase motivation for change, know the costs and benefits of maintaining certain habits and behaviours and the costs and benefits of change, decide what relevant aspects of their day they should change, and learn to set specific and manageable goals to achieve the changes proposed.

#### M2. Nutrition and physical activity education

Its aim is to help participants to reflect on the benefits of eating well, obtain general information about the composition of foods, learn what physical activity is and differentiate it from exercise or sport, understand the role of physical activity in changing one’s lifestyle and weight loss, and have the initial keys to start being more active in everyday life.

#### M3. Strategies to overcome barriers

This aims to identify possible barriers and obstacles to healthy eating and physical activity, provide general information related to intake behaviours and learning little tricks, make participants aware of the importance of breakfast and helping them learn about the difference between different types of exercise, the recommended amount of physical activity, and the advantages and disadvantages of practicing at different times of the day, and making them reflect on the barriers that may be keeping them from starting to perform physical exercise and eating well.

